
### 2.2 Adopted study approach and justification

Notwithstanding the limitations of matching studies noted in the previous section, after careful consideration of the alternatives, a standard PTO choice-experiment incorporating deliberation and discussion was elected as our principal method. The reasons for its advantage in this context are detailed below.

The approach adopted aims to isolate a ‘pure’ youth effect from other aspects of value, as other attributes are held constant between the choices (e.g. the health gain is always identical between choices). This approach places the primary trade off we are interested in as the focus of the respondents’ attention. Whilst we acknowledge other treatment and patient characteristics may be relevant to the social value attributed to the health gain incorporating all these would remove the focus from our question of interest.

The questions present a simpler choice for participants than a DCE in which multiple aspects of the program, treatment or patient could be used as attributes. The simpler PTO choice will help the qualitative components of the study to remain focused on the issue of patient age.

In this study, we wish to capture the views of members of the public of all age ranges. This is important because each age group may feel differently about prioritising patients of their own age. We considered participants’ age of 16 years to be an appropriate benchmark in terms of maturity, literacy and comprehension. At 16 years, participants should have the ability to both consent to the research and have the capacity to understand the questions relating to healthcare prioritising. The desire to include adolescents (16–18 years) in the study further influenced our preference for the simplest style of question used in PTO.

A further advantage of PTO questions is the ability to include individual level comparisons between different types of questions into a survey. Respondents’ inconsistencies can also be discussed with them in the qualitative component.

Two qualitative components will complement the quantitative data collection, one based on an extended cognitive debrief/‘think aloud’ approach in one-to-one interviews (about 40 interviews) and one based on focus groups with deliberation (about 4 focus groups). In both cases these will be with members of the public (the details of these samples are discussed in 2.6 below).

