### 2.4 Qualitative and deliberative component

#### 2.4.1 Qualitative ‘think aloud’ interview alongside PTO; aims and outline

The interviews will complement the quantitative PTO survey and support the main aims of the study shown in Box 1. Specifically, they will seek to:

understand how respondents approach the PTO questions, for example, which information do they focus onexplore whether they think the PTO questions can identify the relative weight they would give to improving child versus adult healthunderstand respondents’ reasons behind their preferencesunderstand any seeming inconsistencies between attitudinal questions and PTO responsesunderstand how strongly views are held through subjecting respondents’ opinions and responses to alternative views and disagreementhelp interpret online survey findings.

To gain most value from the qualitative work, some interviews will occur prior to the main online data collection (hence can support the pilot and be a final opportunity to improve the survey design) and some will occur after the initial data analysis (hence can explore any topics arising from the main online study). The one-to-one interviews will explore how respondents interpret and respond to the PTO questions through encouraging respondents to talk about the questions (‘thinking aloud’) whilst completing the survey. The interviewer will raise the fact that other people hold different or opposing views to explore the reaction to this indirect disagreement. The interviewer will highlight any potential inconsistencies within their responses which may shed light on any inconsistencies between attitudinal questions and PTO responses. The one-to-one interview prompts can be found in the S2 File. The interview protocol and risk management strategy can be found in the S3 File.

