#### 2.5.3 Sample size plan for 1 to 1 ‘think aloud’ interviews and focus groups

We anticipate saturation to be reached at a sample of 40 one-to-one interviews which is fairly large for qualitative research [53]. This should enable sub-samples to be considered including i) parents with young (< = 10 years) children, ii) parents with older children (>10 years), iii) young people (participants aged 16–24), and iv) adults without children. Given the tight focus of the interviews on participant views on one aspect of health care prioritisation only i.e. age, the assumption of saturation at this sample size seems reasonable.

Saturation here will adopt the approach of Guest et al (2020) [54] and “refers to the point during data analysis at which incoming data points (interviews) produce little or no new useful information relative to the study objectives” (p.5). A minimum (base size) of five interviews will be conducted for each sub-group, with a consideration after each additional two interviews (run size) as to whether new information or themes have been gained.

We will hold about four focus groups, each containing a maximum of 5 respondents to encourage in-depth discussion and participation. Our Consumer Advisory Group recommended very careful management of the participant experience given the sensitive nature of the topic and the inclusion of parents with sick children. In response to this concern, focus groups will be conducted with researchers available to provide the option of participants moving to a one-to-one interview should they prefer. Limiting the number of participants per group risks low attendance. However, as participants will have made arrangements to attend the session, the discussion will go ahead with any participants who attend. Low attendance may change the nature of the discussion and will be reflected upon during the data analysis.

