#### 2.6.3 Recruitment plan for one-to-one interviews and focus group

The qualitative work will purposefully target parents and non-parents, different age groups including young people (> = 16 years), and parents of children with a health problem. Recruitment will be via two mechanisms. The first sample will be recruited through a commercial company, CRNRSTONE (https://crnrstone.com.au/). This sample will be biased towards adolescents and adults who do not have children (< = aged 24), and adults who do not live with children, and will cover a mix of gender and ages. The second sample will recruited by following up on participants from a related earlier study (also funded from the QUOKKA MRFF project, referred to as the P-MIC study [55] who have consented to be contacted for future research (n = 984) (https://www.quokkaresearchprogram.org/research-1). This sample will only be parents or carers of children under 18 years old. Recruitment will continue until qualitative saturation has been achieved.

For the qualitative component, interviews will be arranged either by research staff or by the commercial recruitment agency. A reminder about the interview will be sent the day before.

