We will explore the uncertainty around the ROM and MOIR using bootstrapping of the pairs of assigned values described above. We will use 1000 replications with replacement to calculate the percentile confidence interval (CI 2.5%, 97.5%). Other approaches will be explored depending upon the skew of the bootstrap data.

The data collected alongside the qualitative interviews will be combined with the main dataset.

Results of the test of chaining of responses will be considered by comparing the predicted equivalence value (from the chained PTOs e.g. age 2 vs age 12 and age 12 vs age 40) to the related actual equivalence value (e.g. age 2 vs age 40). The predicted (from chained PTO questions, see Table 1A) and actual values will be shown in a scatter plot. We will categorise respondents into meeting or not meeting the chaining test based on whether they display a preference reversal or if the estimate equivalence group size and the actual group size have a difference of 20 or more people (alternative thresholds will be considered). We will use logit regression to explore whether not meeting the chaining test is related to respondent characteristics or other indicators of data quality.

For each age comparison, we will report ratio of the means and median of the individual ratios, for the 5 health contexts. T-tests will be used to determine if the mean of the ratios is statistically significant different between two study arms (offering a choice of equivalence vs not offering the choice of equivalence), and Wilcoxon’s U-test will be used to determine if median values are statistically significantly different between two arms. An example of how the data will be presented is shown in S4 Table. T-tests will be used to determine if the mean of the ratios value is statistically significantly different between two contexts comparing a health gain of 5 years versus 2 years, and Wilcoxon’s U-test will be used to determine if median values are statistically significantly different. Kruskal-Wallis H tests will be used to determine if the ratios are statistically significantly different between the three contexts across relieving pain, mobility problems and emotional problems.

We will produce histograms showing the distribution of equivalence values for each age comparison; combined, and separately for the forced (dichotomous) and unforced (offering equivalence choice) modes.

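### Answers from about 40 purposively recruited think-aloud interviewees are pooled into the dataset that estimates the Australian public's weights: a small effect, but avoidable at almost no cost

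*Protocol article*

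**What the plan says.** The pooling rule is in section 2.7.3, directly after the definitions of ROM and MOIR and the bootstrap: "The data collected alongside the qualitative interviews will be combined with the main dataset". The Introduction gives the target of those estimates as the average relative weight in the judgement of the Australian general public.

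The two groups of respondents differ in three ways.

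- **Recruitment.** Online respondents may enter only while their age/gender, education and location quotas are open (section 2.6.2). No such quota is stated for interviewees. Section 2.6.3 says: "The qualitative work will purposefully target parents and non-parents". It describes the first source thus: "This sample will be biased towards adolescents and adults who do not have children". Of the second source, participants in a related earlier study, it says: "This sample will only be parents or carers of children under 18 years old".
- **Mode.** The interviews work by "encouraging respondents to talk about the questions (‘thinking aloud’) whilst completing the survey" (section 2.4.1). The same section adds: "The interviewer will raise the fact that other people hold different or opposing views to explore the reaction to this indirect disagreement".
- **Timing and number.** Section 2.4.1 places some interviews before the main online collection and some after the initial data analysis. Section 2.5.3 says: "We anticipate saturation to be reached at a sample of 40 one-to-one interviews". Section 2.6.3 keeps recruitment open until saturation.

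The methods factors named for the multinomial regression in section 2.7.3 are screen side and forced or unforced choice. The sensitivity analyses in section 2.7.2 concern rapid completion and low comprehension. Neither list mentions data source.

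**The concern.** The main estimate is meant to describe a population, and the online quotas are the plan's device for getting there. Adding purposively chosen people works against that device. Section 2.6.1 itself says that age, gender and parent status affect the relative value given to child health, and interviewees are selected on two of these.

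The mode also differs, and part of the added data arrives once initial results are known. The number added depends on thematic content, not on a statistical target. At stake is a clean description of whom the weights represent and how the answers were obtained. Large numerical bias is not the issue.

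**Working it through.** **1. The plan's own figures.** Section 2.5.2 has 13 young ages and 2 adult ages.

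- Comparisons: 13 × 2 = 26.
- Minimum surveys: 50 × 26 = 1,300, as stated.
- Per arm and comparison: 1,000/26 = 38.5, stated as 38.
- Both arms together: 2,000/26 = 76.9 per comparison.

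The 38 comes from the online sample alone and does not depend on the interview data.

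**2. Share of interview data.**

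- With 40 interviews: 40/(2,000 + 40) = 0.0196, or 2.0%; 40/26 = 1.5 per comparison.
- With 20 interviews (the minimum of five in each of the four sub-groups of section 2.5.3): 20/2,020 = 0.0099, or 1.0%.

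**3. Shift in ROM.** Section 2.7.3 scores the preferred group 1 and the other group as the preferred group's size at indifference divided by 100. ROM is the ratio of the two mean scores. With weight w = 0.0196 on interviewees,

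pooled ROM = [(1 − w)·a + w·a′] / [(1 − w)·b + w·b′],

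where a and b are the online means for the younger and older group, and a′ and b′ are those of the interviewees. The article gives no expected means, so all of these are assumptions. The extreme score 0.005 is Table 2's 0.5 divided by 100.

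| Online a, b | Online ROM | Interviewees a′, b′ | Pooled ROM | Shift |
|---|---|---|---|---|
| 0.95, 0.75 | 1.267 | 1, 0.5 | 1.276 | +0.010 |
| 0.95, 0.75 | 1.267 | 1, 0.005 (all extreme pro-young) | 1.293 | +0.027 |
| 0.95, 0.75 | 1.267 | 0.005, 1 (all extreme pro-adult) | 1.234 | −0.033 |
| 0.90, 0.85 | 1.059 | 1, 0.5 | 1.070 | +0.011 |
| 0.90, 0.85 | 1.059 | 1, 0.005 | 1.082 | +0.023 |
| 0.90, 0.85 | 1.059 | 0.005, 1 | 1.035 | −0.024 |

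**4. Precision for comparison.** With assumed standard deviations of 0.15 to 0.30 for the scores, the 95% half-width of ROM in one comparison at n = 77 is about 0.09 to 0.13. For example, with means 0.95 and 0.75, standard deviations 0.15 and 0.30 and no correlation:

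1.96 × 1.267 × √[((0.15/0.95)² + (0.30/0.75)²)/77] = 0.12.

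If an all-ages average is also reported, the same assumptions at n = 2,000 give 0.12 × √(77/2,000) = 0.024. The moderate shift of 0.01 is under half of that; the bounding cases are of similar size to it.

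**5. Uneven spread.** If 40 interviewees fall at random over 26 comparisons, simulation puts about four in the fullest one (5th to 95th percentile 3 to 6). With 77 online respondents at 0.95 and 0.75 plus four interviewees at 1 and 0.5:

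(77 × 0.95 + 4 × 1)/(77 × 0.75 + 4 × 0.5) = 77.15/59.75 = 1.291, a shift of 0.025.

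If all four are extreme, the results are 77.15/57.77 = 1.335 and 73.17/61.75 = 1.185, shifts of +0.07 and −0.08. These lie within the half-width of about 0.12 for that comparison.

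**6. Fit with the entry rules.** Section 2.10.1 makes entry to the main dataset conditional on criteria that include a survey-company ID and a minimum time based on online completion. Section 2.11.3 links interview survey data only by the timing of the interview. The article does not say how the entry rules apply to interviewees.

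**The case against.** The strongest defence is size: 2% of the data cannot move any planned result materially, as the working shows. Other points also count.

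- Section 2.3.18 cites a comparison that found no significant difference in PTO values between face-to-face and web administration.
- The online sample is itself a commercial panel with loose geographic quotas and no parenthood quota.
- The two interview sources lean in opposite directions on parenthood.
- A condensed article may leave a with-and-without analysis to a fuller plan.

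The size argument stands and limits the point. The mode evidence helps only in part, because it does not concern thinking aloud. The absence of a sensitivity analysis would not be a finding on its own. The pooling rule, however, is stated outright and not left open.

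Two stronger readings are tempting, and the documents do not support them.

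- **That PTO answers are given under interviewer challenge.** Section 2.2 has the interviewer feed back the respondent's weights, which requires answers already given, and places reconsideration after the discussion. Section 2.3.12 puts the attitudinal questions after the PTO, so inconsistencies between the two can be raised only once PTO answers exist. The order is not fully explicit, and the article does not say whether original or revised answers are pooled. Contamination is therefore an inference.
- **That answers to a superseded survey are freely mixed in.** Section 2.9.4 keeps the six recruited pilot interviews only if no substantial changes follow, and excludes the two convenience pilot interviews. Section 2.9.2 excludes the online-survey pilots.

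**Conclusion.** The point holds as a matter of sampling frame, mode and timing, with a small expected effect. About 2% of the pooled respondents would come from outside the quotas, selected partly on characteristics that the article says influence preferences, and some after initial results are known. The expected shift in an overall ROM is about 0.01, and at most about 0.02 to 0.03 with every interviewee at the extreme. These sizes rest on the assumed means and on 40 interviews; fewer interviews would shrink them. A single comparison could be affected more by chance.

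A reader might also infer a marked distortion among parents of a child with a health condition, where interviewees may be concentrated. The article does not support a figure for this. It gives neither the size of that subgroup nor the number of interviewees in it. It also lists no ROM for the subgroup: respondent differences go through the regression on preference class.

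The change is still worth making, because pooling gains almost nothing and blurs whom the main estimate describes.

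**What to change.** In section 2.7.3, replace the pooling sentence with a rule that the main ROM, MOIR, forced-versus-unforced tests and regressions use the online quota sample (n = 2,000). Keep a data-source flag on every record. Report the pooled result as a sensitivity analysis, using the PTO answers recorded before any interviewer challenge, and state that revised answers serve the qualitative aims only. Retain the existing condition on the six recruited pilot interviews for that sensitivity analysis.

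The cost is a sentence or two of text and about 2% fewer responses in the main estimates (2,000 instead of 2,040). The stated 38 per arm and comparison is unaffected.

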#### 2.3.11 Testing data quality and the stability of preferences

Internal consistency of responses can be assessed by tests of cardinal transitivity [46], which is also referred to as ratio consistency, multiplicative transitivity or triad consistency. An individual’s PTO equivalence value for ages 10 versus 20 and 20 versus 30, for example, should accurately predict their PTO equivalence value for age 10 versus age 30. To test this at an individual level requires individuals to be asked at least three questions which ‘chain’ together.

Internal consistency may be judged by comparing PTO answers against other methods for eliciting aged-based preferences such as opinion questions and ranking. However, past evidence suggests fairly systematic differences across research methods with ranking more often being linearly related to age, and opinion surveys responses more likely to reflect a preference for equal treatment [11]. Therefore, these indirect comparisons cannot say much about data quality.

This survey will include an attention check question, consistency comparisons to screening data based on personal demographic data and a minimum time to complete, all of which aim to exclude responders who are not engaged with the survey. We will also consider consistency comparisons to attitudinal questions, but these will not be treated as strict quality checks since there may be legitimate reasons for these differences.

A ratio test will be undertaken for one of the years of life extension questions by chaining PTO values. Each respondent will answer the main PTO questions for just one age. For the question relating to life extension of 2 years they will answer two additional chaining questions i) their given age compared to an age which is either higher or lower by 10 years, as shown in Table 1A, and ii) this age compared to aged (40 or 55), as shown in Table 1B. The expected PTO value will be calculated for each individual based on the two PTO equivalence values (Age X vs (40 or 55)) x (Age Y vs (40 or 55)) and this will be compared to the actual equivalence value (Youngest from X or Y vs (40 or 55)). For example, if the respondent is given age 8 for their PTO questions, they will be asked to complete a PTO comparing patients of ages 8 vs (40 or 55). They will also be asked to compare ages 8 vs 18 and ages 18 vs (40 or 55). The product of the last two responses (the expected value) will be compared to the ages 8 vs (40 or 55) response (the actual value).

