#### 2.3.12 Order effects and randomisation of question order

Order effects may arise through learning effects which result in respondents giving more accurate preferences in later questions and through respondent fatigue which may result in less attention being given to later questions. The order of questions may also generate framing effects leading respondents to focus on certain aspects of the choice–for example asking a question about children leading short lives first may lead people into considering length of life even during questions on quality of life. Earlier questions may draw respondents’ attention to differences between temporary versus permanent health gains [47]. Ubel et al., (2001, 2002) [48,49] identified strong order effects in PTO questions both from numerical anchoring from the group sizes in earlier questions and from questions which make people think about equity considerations and avoiding discrimination. To avoid ordering effects, this study will randomise the order of the PTO question, although the survey will avoid switching question types (e.g. between life extension and quality of life improvement) so as not to add to respondent burden. Participants will be randomised to receive either the life extension questions first (4 questions shown in random order) or the quality of life enhancing questions (3 questions shown in random order) first. The attitudinal and opinion survey questions will follow the PTO to try and avoid further focusing effects. We will test the impact of participants seeing life extension or quality of life enhancing questions first.

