**Fig 10 pone.0302886.g010:**
[figure not shown]
Visual display of the percentage choosing equivalence at each group size comparison.

We will categorise respondents into seven classifications for each context according to their preferences as set out in Table 3.

**Table 3 pone.0302886.t004:** Preference classification based on PTO responses.

Classification	Threshold
Extreme preference for younger age group	Prefers to treat 1 younger age group than 100 older age group
Strongly prefer younger age group	Equivalence group size between 1 and 50 of younger age group equivalent to 100 of the older age group
Weakly prefer younger age group	Equivalence group size greater than 50 of younger age group equivalent to 100 older age group
Equal preference	Expresses equivalence when group sizes are the same or prefers to treat 100 of not preferred age group than 95 of the preferred age group
Weakly prefer older age group	Equivalence group size greater than 50 of older age group equivalent to 100 younger age group
Strongly prefer older age group	Equivalence group size between 1 and 50 of older age group equivalent to 100 of the younger age group
Extreme preference for older age group	Prefers to treat 1 older age group than 100 younger age group

Multinomial logistic regression analyses will be used to explore whether the individual’s classification from their PTO responses (either based on Table 3 or simplified to three classifications) is associated with respondent characteristics and the age/context of the PTO question. This will treat the within childhood age comparisons (that are included in the chaining tests) separately to comparisons between children and adults.

Controls will include ages used in the PTO question, type of health gain, respondent demographic characteristics, and methods factors (whether the younger age appears on the left or right of the screen, forced or unforced preference). Alternative approaches to addressing the fact that individuals complete more than one PTO question will be explored including clustering standard errors and random effects multinomial logistic models.

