#### 2.7.4 Comparing PTO values to attitudinal questions

We will present the percentage of potentially inconsistent responders based on the rules in Table 4. These will be interpreted cautiously as there may be legitimate reasons for apparent contradictions.

**Table 4 pone.0302886.t005:** Identification of potentially inconsistent responders.

	Which of these statements best reflects your views?	Potentially inconsistent responses
1	For medical care that improves quality of life temporarily, children should have some priority over adults.	For any of the 3 quality of life questions relative weights suggests equal value or a pro-adult preference.
2	For medical care that improves quality of life temporarily, adults should have some priority over children.	For any of the 3 quality of life questions relative weights suggests equal value or a pro-child preference.
3	People should have the same priority with respect to medical care that improves quality of life temporarily, regardless of age.	For any of the 3 quality of life questions relative weights suggests a pro-adult or pro-child preference.
4	For medical care that extends life children should have some priority over adults.	For any of the life extension questions relative weights suggests equal value or a pro-adult preference.
5	For medical care that extends life adults should have some priority over children.	For any of the life extension questions relative weights suggests equal value or a pro-child preference.
6	People should have the same priority with respect to medical care that extends life regardless of age.	For any of the life extension questions relative weights suggests a pro-child or pro-adult preference.
7	This is fair because they are children	For any of the 7 PTO questions relative weights suggests equal value or a pro-adult preference.
8	This would make me feel concerned	For any of the 7 PTO questions relative weights suggests a pro-child preference.
9	This would be unfair	For any of the 7 PTO questions relative weights suggests pro-child preference.

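### Section 2.7.3 names independent-groups rank tests for the 2- versus 5-year and pain/mobility/distress comparisons, although the same respondents answer all of these questions

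*Protocol article*

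**What the plan says.** **Who answers what.** Section 2.3.11 states: "Each respondent will answer the main PTO questions for just one age". Section 2.3.12 gives both blocks to everyone and randomises only which comes first: "Participants will be randomised to receive either the life extension questions first (4 questions shown in random order". In the alternative order, the block of three quality-of-life items leads. The four life-extension questions are the 2-year question, the 5-year question and the two chaining questions of section 2.3.11. Table 4 in section 2.7.4 confirms the total at respondent level: "For any of the 7 PTO questions relative weights suggests equal value or a pro-adult preference".

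**Which tests are named (section 2.7.3).**
- Forced versus unforced arms: t-test for means, Wilcoxon's U-test for medians.
- 2 versus 5 years, means: "T-tests will be used to determine if the mean of the ratios value is statistically significantly different between two contexts". Paired or unpaired is not stated.
- 2 versus 5 years, medians: Wilcoxon's U-test again, for values "different between two contexts comparing a health gain of 5 years versus 2 years".
- Three quality-of-life domains: "Kruskal-Wallis H tests will be used to determine if the ratios are statistically significantly different between the three contexts".

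**Where repeated answers are recognised.** Later in section 2.7.3, for the multinomial regression of preference classes, clustered standard errors and random effects are to be explored because of "the fact that individuals complete more than one PTO question". Nothing similar is said for the tests above.

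**The concern.** The duration contrast (aim 2c) and the domain contrast (aim 2b) compare answers given by the same people about the same age pair. The U-test (rank-sum) and Kruskal-Wallis H treat those answers as coming from separate people. Someone who strongly favours the young in one question is likely to do so in the next. The variation between people then stays in the error term, although comparing each person with themselves would remove it.

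False positives are not the risk here. The risk is that a real dependence of the child weight on the type or duration of gain goes undetected, and that a non-significant result is read as support for one weight across contexts.

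**Working it through.** **1. Respondents per comparison.** There are 13 young ages × 2 adult ages = 26 age pairs (section 2.5.2). The stated minimum reproduces: 26 × 50 = 1300. The stated 38 per arm reproduces: 1000/26 = 38.5. Both arms together give 2000/26 = 76.9, about 77 per age pair.

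**2. Matching test to design.**

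| Contrast | Groups in the design | Test named | Fit |
|---|---|---|---|
| Forced vs unforced | Different people, randomised | t-test, U-test | Right |
| 2 vs 5 years, median | Same people | U-test | Assumes independence |
| 2 vs 5 years, mean | Same people | t-test, type not stated | Unspecified |
| Pain/mobility/distress | Same people | Kruskal-Wallis H | Assumes independence |

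Using the U-test label for the randomised arms as well makes it unlikely to be a loose name for the signed-rank test.

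**3. Size of the effect for two contexts (normal approximation).** Assumptions, none of them in the document: two-sided 5% level (the article gives only 2.5% and 97.5% bootstrap limits), 80% power for a correctly paired test, equal variances, within-respondent correlation ρ.

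The true standard error of the mean difference is σ√(2(1−ρ)/n). The independent-samples formula uses σ√(2/n), which is too large by 1/√(1−ρ). The unpaired test therefore rejects only when the correctly scaled statistic exceeds 1.96/√(1−ρ). With 80% paired power, that statistic is centred at 1.96 + 0.84 = 2.80. Hence:

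- true level = 2[1 − Φ(1.96/√(1−ρ))]
- power = Φ(2.80 − 1.96/√(1−ρ))

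Example, ρ = 0.5: 1.96/0.7071 = 2.77; level = 2[1 − Φ(2.77)] = 0.56%; power = Φ(0.03) = 51%.

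| ρ | True level | Power (paired test = 80%) |
|---|---|---|
| 0 | 5.0% | 80% |
| 0.2 | 2.8% | 73% |
| 0.3 | 1.9% | 68% |
| 0.5 | 0.56% | 51% |
| 0.6 | 0.19% | 38% |
| 0.7 | 0.03% | 22% |
| 0.8 | 0.001% | 6% |

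More than half of the 80% is lost only when ρ is above about 0.6.

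**4. Simulation of the rank tests.** Correlated normal log ratios (SD 1, mean 0.3) were rounded to the mid-point grid of Table 2, with n = 77 and 1000 runs. The two-context shift was d = 2.80√(2(1−ρ)/n). The three-context shifts were 0, d/2 and 1.1d. Power:

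| ρ | U-test | Signed-rank | Kruskal-Wallis | Friedman |
|---|---|---|---|---|
| 0 | 80.0% | 80.9% | 76.9% | 65.3% |
| 0.3 | 63.5% | 75.9% | 58.6% | 65.4% |
| 0.5 | 46.9% | 76.7% | 36.6% | 65.7% |
| 0.7 | 22.7% | 77.3% | 10.8% | 65.2% |
| 0.8 | 5.4% | 73.7% | 1.8% | 68.5% |

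With no true difference at ρ = 0.5, the rejection rates were 0.9% (U-test), 5.6% (signed-rank), 0.2% (Kruskal-Wallis) and 5.1% (Friedman). Results at n = 38 follow the same pattern. At ρ = 0, Friedman is weaker than Kruskal-Wallis.

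**The case against.** The best defence has four parts.

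- **The correlation is unknown.** A reader might infer that these tests lose most of their power. The document does not support that. At ρ = 0.2 or 0.3 the loss from 80% is about 7 or 12 points, and only above about 0.6 does it exceed half. High correlation is plausible (same person, same ages, same 100-versus-100 start), but it is an assumption. This part stands.
- **The t-test may be paired.** A reader might also infer that the t-test for duration is wrong. The article does not say it is unpaired, so the fault there is an open choice. This part stands too.
- **The multinomial model is a safeguard.** It includes type of gain, is not confined to one age pair and may account for clustering. So conclusions about context do not rest on the named tests alone. The safeguard is partial: its outcome is preference class rather than the ratio, and its handling of clustering is still to be explored. Section 2.7.3 says the ratio of means and median of ratios will themselves be compared between types of gain.
- **Aim 2a has no named test.** A reader might count this as a further error. It is detail that an article may leave to a fuller plan, and no wrong method is stated for length versus quality of life.

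None of this makes the U-test or Kruskal-Wallis suitable for repeated answers, and nothing elsewhere in the article corrects them.

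**Conclusion.** The point holds for two stated methods: the U-test for 2 versus 5 years and Kruskal-Wallis H for the three domains. Both ignore that the answers come from the same respondents. With positive correlation they are conservative and lose power for aims 2b and 2c. The unpaired counterpart of an 80%-power paired test has between about 73% (ρ = 0.2) and 6% (ρ = 0.8). Those figures rest on an assumed 5% level, the normal approximation for two contexts and a correlation that the document does not give.

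This should be fixed, but it does not undermine the study. The error runs towards missing differences rather than inventing them. The aim 1 weights, their per-context bootstrap intervals and the forced-versus-unforced test do not depend on it.

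**What to change.** - **2 versus 5 years:** use the Wilcoxon signed-rank test, or a bootstrap that resamples whole respondents for the between-context difference in ratio of means and median of ratios. The bootstrap addresses the planned summary measures directly, whereas signed-rank tests within-person differences. State that the t-test is paired.
- **Three domains:** use the Friedman test, a respondent-level bootstrap, or a mixed or clustered model. The last two are sound choices if correlation could be near zero, where Friedman can be weaker than Kruskal-Wallis.
- **Length versus quality of life (aim 2a):** treat any such contrast as paired in the same way.
- **Forced versus unforced:** keep the independent-groups tests.

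The cost is a change of wording and analysis code. No additional respondents, questions or data are needed, and the change can be made before analysis.
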